## Abstract

**Background:**

Post-stroke cognitive impairment (PSCI) is common and hampers rehabilitation. Dysregulated iron homeostasis and ferroptosis are implicated in PSCI, yet targeted treatments are lacking. Acupuncture may improve cognition, but its early-intervention efficacy and iron-related mechanisms remain unclear.

**Methods and analysis:**

This single-blind randomized controlled trial will enroll 72 patients with ischemic stroke-related cognitive impairment (IS-CI). Participants will be randomized 1:1 to electroacupuncture (EA) or sham electroacupuncture (sEA) in addition to standard pharmacotherapy and rehabilitation. Participants in the EA group will receive verum stimulation at Baihui (GV20), Sishencong (EX-HN1), Shenting (GV24), and bilateral Neiguan (PC6), along with five adjunct points—Hegu (LI4), Zusanli (ST36), Xuanzhong (GB39), Sanyinjiao (SP6), and Taichong (LR3)—on the affected side. The sEA group will receive sham acupuncture at non-acupoint, non-meridian locations situated 1–2 cun away from the true acupoints. Interventions are delivered 5 times weekly for 4 weeks (20 sessions, 30 min each). The primary outcome is the change in Montreal Cognitive Assessment (MoCA) score from baseline to week 4. Secondary outcomes include Mini-Mental State Examination (MMSE), Modified Barthel Index (MBI), Hamilton Anxiety (HAMA) and Depression (HAMD) scales, Pittsburgh Sleep Quality Index (PSQI), and PSCI incidence at 3-month post-stroke (MoCA <26). A prespecified MRI substudy (*n* = 30) will use 3.0 T quantitative susceptibility mapping (QSM) to quantify regional cerebral iron and explore associations between changes in susceptibility and cognitive measures. Participants and outcome assessors are blinded; allocation is concealed; analyses will follow prespecified statistical plans.

**Conclusion:**

This trial is designed to evaluate the effects of EA on cognitive function in patients with IS-CI and to explore whether changes in cognition are accompanied by changes in cerebral iron deposition measured by QSM. It aims to assess the feasibility and preliminary effects of this intervention and to explore iron-related mechanisms in PSCI using an imaging approach.

**Clinical trial registration:**

http://itmctr.ccebtcm.org.cn/, ITMCTR2025001739.

## Introduction

Stroke is a major acute cerebrovascular disease classified into the ischemic and hemorrhagic subtypes. Ischemic strokes constitute approximately 87% of all cases (1). Globally, it remains the second-leading cause of death and third-leading contributor to disability-adjusted life-years (DALYs) (2), while ranking first in mortality and disability in China (3). Cognitive deficits are common after stroke, and a Chinese expert consensus notes that many patients develop post-stroke cognitive impairment (PSCI) by 3-month post-stroke (4). PSCI primarily affects multiple cognitive domains, including executive function, memory, calculation, visuospatial ability, and language (5), with a global prevalence of approximately 44% and a higher prevalence of about 53.1% among Chinese stroke survivors (6, 7). Cognitive deficits are associated with greater disability, dependence, and higher morbidity, placing a substantial burden on patients, caregivers, and healthcare systems (8). Accordingly, early cognitive assessment and timely intervention are considered critical to improving post-stroke rehabilitation outcomes (4).

The pathogenesis of PSCI is complex and multifactorial, involving direct injury to cognition-related brain regions, disruption of structural and functional connectivity, global neural dysfunction due to acute inflammation and neurotoxicity, and reduced overall brain reserve capacity (8). Recent studies have highlighted the role of dysregulated iron homeostasis in PSCI, particularly implicating ferroptosis, an iron-dependent form of programmed cell death, as a major mechanism of post-ischemic neuronal injury (9). Excess iron can promote oxidative stress and ferroptotic cell death, thereby exacerbating neuronal loss and cognitive decline. Reducing cerebral iron accumulation has therefore been proposed as a potential therapeutic strategy for PSCI (9, 10).

In light of the limited treatment options for PSCI, there is growing interest in non-pharmacological interventions such as acupuncture. Acupuncture is one of the oldest and most widely practiced therapies in Traditional Chinese Medicine (TCM) and is endorsed by the World Health Organization (WHO) (11). Recent systematic reviews and meta-analyses have demonstrated that acupuncture can significantly improve cognitive function among stroke survivors (12–14). However, the neurobiological mechanisms underlying these cognitive benefits remain only partially understood. Preclinical studies using electroacupuncture (EA) in rodent models of ischemic stroke suggest that EA exerts neuroprotective effects by modulating ferroptosis-related pathways. Reported mechanisms include restoring iron homeostasis, inhibiting ferritinophagy, activating the nuclear factor erythroid 2-related factor 2 (Nrf2) antioxidant pathway, and upregulating glutathione peroxidase 4 (GPX4) (15–17). Because EA delivers standardized electrical stimulation at defined frequencies and intensities, it may more reliably engage these iron- and redox-related signaling pathways than manual acupuncture in experimental models. Emerging clinical data suggest that acupuncture can modulate the systemic iron status. In a randomized controlled trial (RCT), adjunctive acupuncture enhanced the response to oral iron, producing larger increases in serum iron, transferrin saturation, and hemoglobin, together with marked reductions in leptin and hepcidin compared with sham acupuncture (18). In another study, needling acupoints led to significantly greater improvements in hemoglobin and red blood cell indices than non-acupoint needling (19). Although these trials assess peripheral rather than cerebral iron, they support the translational plausibility that EA can influence iron-related pathophysiology and provide a clinical rationale to investigate its effects on brain iron deposition in PSCI. Nonetheless, direct evidence that acupuncture alters cerebral iron deposition in stroke survivors is still lacking, and no RCT has yet examined the impact of acupuncture on brain iron load using quantitative neuroimaging techniques.

Therefore, to address these gaps, we have designed an RCT that will utilize 3.0 T magnetic resonance imaging (MRI) with quantitative susceptibility mapping (QSM) to precisely quantify cerebral iron load in patients with ischemic stroke-related cognitive impairment (IS-CI). By combining this neuroimaging approach with detailed cognitive assessments, the trial will comprehensively evaluate both the clinical efficacy of EA and its underlying mechanisms in IS-CI. The specific objectives are:

To evaluate the efficacy of EA in improving cognitive function in IS-CI patients;To explore whether EA-related changes in cognition are accompanied by changes in regional cerebral iron deposition quantified by QSM. This imaging approach is intended to provide hypothesis-generating evidence on iron-related mechanisms in PSCI.

## Methods

### Research design

This single-blind, RCT will be conducted in the Department of Rehabilitation Medicine, West China Hospital of Sichuan University (Chengdu, China). A total of 72 inpatients with IS-CI will be randomized 1:1 to receive EA or sham electroacupuncture (sEA). Figure 1 outlines the study flow, and Table 1 details the schedule of enrolment, interventions, and assessments.

**Figure 1 fig1:**
[figure not shown]
Trial flow chart. IS-CI, ischemic stroke-related cognitive impairment; MoCA, Montreal Cognitive Assessment; MMSE, Mini-Mental State Examination; MBI, Modified Barthel Index; HAMD, Hamilton Depression Rating Scale; HAMA, Hamilton Anxiety Rating Scale; PSQI, Pittsburgh Sleep Quality Index; PSCI, post-stroke cognitive impairment.

**Table 1 tab1:** Details of the planned visit schedule.

	Study period					
	Baseline (*n* = 72)	Treatment (*n* = 72)				Follow-up (*n* = 72)
Timepoint	0	Week 1	Week 2	Week 3	Week 4	3 Months after onset
Enrollment						
Eligibility screen	×					
Informed consent	×					
Demographic characteristics	×					
Medical history	×					
MRI	×					
Interventions						
Electroacupuncture group		×	×	×	×	
Sham-electroacupuncture group		×	×	×	×	
Assessments						
MoCA	×				×	×
MMSE	×				×	
MBI	×				×	
HAMA	×				×	
HAMD	×				×	
PQSI	×				×	
PSCI incidence						×
Patient safety						
Adverse events		×	×	×	×	

The study received ethics approval (no. 2025-1209) from West China Hospital of Sichuan University on 7 July 2025 and was registered on the International Traditional Medicine Clinical Trial Registry Platform (ITMCTR; registration number: ITMCTR2025001739) on 15 September 2025.

### Diagnostic criteria

Ischemic stroke will be diagnosed according to the 2019 American Heart Association/American Stroke Association (AHA/ASA) Guidelines (20) and the Chinese Guidelines for Acute Ischemic Stroke (2023) (21). Cognitive impairment will be established with reference to the 2023 AHA/ASA scientific statement *“*Cognitive Impairment After Ischemic and Hemorrhagic Stroke*”* (5) as a Montreal Cognitive Assessment (MoCA) score below 26.

#### Inclusion criteria

Inclusion criteria include:

Meets both stroke and cognitive impairment definitions;Aged 18–75 years, either of sex;Ischemic stroke onset 7–30 days before enrolment;MoCA < 26 and able to cooperate with acupuncture and assessments;Stable vital signs;National Institutes of Health Stroke Scale (NIHSS) score 1–15;Written informed consent from the patient or legal guardian.

#### Exclusion criteria

Exclusion criteria include:

Unstable vital signs or uncontrolled severe cardiopulmonary disease;Previous stroke;Pre-existing cognitive impairment, depression, or other psychiatric disorders;Malignancy, significant hematological disorder, respiratory failure, or active infection;Severe dysfunction of other organs or critical systemic diseases;Severe visual/hearing impairments or aphasia precluding cooperation;Imaging subgroup only: MRI contraindications (metallic implants/electronic devices) or left-handedness.

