### MRI data acquisition

All MRI examinations will be performed at the MRI Center of West China Hospital, Sichuan University, on a 3.0 T scanner (Discovery MR750; GE Healthcare, Milwaukee, USA) equipped with an eight-channel phased-array head coil. Before each examination, participants will be instructed to minimize head motion, and their heads will be stabilized with foam pads. Scans will be acquired with the participant lying supine and remaining alert throughout. After acquisition, two trained neuroimaging analysts will visually inspect the magnitude and phase images for artifacts, including motion, signal dropout, and severe susceptibility distortions. Datasets with pronounced motion artifacts that preclude reliable phase unwrapping will be repeated where feasible; if repetition is not possible, the scan will be excluded from QSM analyses, and the reason will be documented.

A high-resolution structural dataset will be obtained with a three-dimensional T1-weighted spoiled gradient-echo sequence (TR/TE = 6.2/2.5 ms, field of view = 256 × 256 mm^2^, data matrix = 256 × 256, voxel size = 1.0 × 1.0 × 1.0 mm^3^). QSM will be derived from a gradient-recalled echo sequence (flip angle = 17°, field of view = 229 × 229 mm^2^, voxel size = 0.7 × 0.7 × 4.0 mm^3^, number of slices = 52, slice thickness = 4 mm).

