### Neuroimaging data analysis

We will process the GRE data to generate QSM maps using the standard pipeline implemented in the SuscEptibility mapping PIpeline tool for phase (SEPIA) images toolbox run under MATLAB (MathWorks, Natick, MA), following established methodologies (38). Whole-brain magnitude images will be skull-stripped using the BET tool from the FMRIB Software Library, integrated within the MEDI toolbox. The overall procedure consisted of three main steps: (1) Total field recovery will be achieved through echo phase combination via the optimum weights method (39), followed by phase unwrapping using SEGUE (40). (2) Background field removal will then be performed on the unwrapped phase images by applying the Laplacian boundary value approach (41). (3) Finally, quantitative susceptibility maps will be reconstructed using the STAR-QSM algorithm for dipole inversion (42).

Region-of-interest (ROI) definition and extraction will follow an *a priori*, region-based approach. We will focus on deep grey matter and limbic structures that are susceptible to post-stroke iron accumulation and implicated in cognition, including the bilateral caudate nucleus, putamen, globus pallidus, thalamus, hippocampus, red nucleus, substantia nigra, and dentate nucleus, informed by previous QSM studies of brain iron and clinical outcomes (43–46). For each participant, the T1-weighted structural image will be co-registered to the QSM map, and subcortical ROIs will be segmented using a standard atlas-based method implemented in FSL. The resulting ROI masks will be resampled into QSM space and visually inspected. Mean susceptibility values (ppm) within each ROI will be extracted at baseline and at week 4. All registrations and ROI segmentations will be visually checked by two independent neuroimaging analysts. Any discrepancies will be resolved by consensus, and if necessary, the processing pipeline will be refined before final extraction. All image preprocessing and QSM analyses will be performed on de-identified datasets that are coded by study ID, and the analysts will remain blinded to treatment allocation and clinical outcome data until the primary analyses have been completed.

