Iron is an essential micronutrient in the brain, involved in neurotransmitter synthesis, myelin formation, and mitochondrial energy production (54, 55). However, ischemic stroke can disrupt iron homeostasis, resulting in excess iron accumulation in affected and connected brain regions and triggering iron-dependent oxidative neurotoxicity (ferroptosis) (56, 57). Radiological and histopathological studies have demonstrated progressive iron deposition in structures such as the ipsilateral thalamus, substantia nigra, and basal ganglia after stroke, and higher post-stroke iron burden in deep grey matter has been linked to poorer neurological outcomes (57–59). The degree of post-stroke iron accumulation in these regions correlates with worse neurological outcomes (56, 58, 59). These observations support cerebral iron overload as a clinically relevant, potentially modifiable factor in post-stroke recovery and provide a rationale to investigate brain iron as a mechanistic target in PSCI.

QSM is a gradient-echo based MRI post-processing technique that reconstructs tissue magnetic susceptibility maps from phase images. Because paramagnetic iron is a major source of susceptibility contrast in the brain, higher QSM values closely reflect increased regional iron content and have been widely used to characterize iron accumulation in brain aging, neurodegenerative diseases, and cerebrovascular disorders (44, 60, 61). In patients with acute IS, a recent QSM study reported that higher iron content in deep grey matter nuclei was associated with poorer functional outcome (43), supporting cerebral iron burden as a clinically meaningful imaging marker in this population. These advances indicate that QSM provides a quantitative and relatively specific *in vivo* measure of brain iron load, making it particularly suitable for testing ferroptosis-related hypotheses in PSCI. However, the magnitude and time course of intervention-related changes in QSM after stroke are not yet established in humans. In this trial, QSM outcomes will therefore be treated as exploratory mechanistic markers to provide effect-size estimates and generate hypotheses.

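### Regional susceptibility is a plain mean over deep-grey regions that may contain the index lesion, with no lesion handling and no alignment to lesion side

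*Protocol article*

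**What the plan says.** Inclusion criteria (Protocol article) set the timing, "Ischemic stroke onset 7–30 days before enrolment", and place no limit on lesion site. Under Exclusion criteria, the imaging-specific items are "Imaging subgroup only: MRI contraindications (metallic implants/electronic devices) or left-handedness". Neither they nor the general criteria mention infarct location or haemorrhagic change.

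Neuroimaging data analysis names the regions, "including the bilateral caudate nucleus, putamen, globus pallidus, thalamus, hippocampus, red nucleus, substantia nigra, and dentate nucleus", segments them with an atlas, and defines the measurement: "Mean susceptibility values (ppm) within each ROI will be extracted at baseline and at week 4". The check on the masks is "The resulting ROI masks will be resampled into QSM space and visually inspected", done by two analysts blinded to allocation.

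Under MRI data acquisition, analysts "will visually inspect the magnitude and phase images for artifacts, including motion, signal dropout, and severe susceptibility distortions". The stated trigger for action is motion: "Datasets with pronounced motion artifacts that preclude reliable phase unwrapping will be repeated where feasible", and otherwise the scan is excluded.

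The imaging tests are paired and independent-samples t-tests and Pearson or Spearman correlations of changes, with false-discovery-rate correction across regions. Lesion side, territory and volume, and thrombolysis, appear only under Clinical data analysis, as optional candidate covariates for sensitivity analyses. The Discussion bases its rationale on "progressive iron deposition in structures such as the ipsilateral thalamus, substantia nigra, and basal ganglia after stroke".

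**The concern.** The substudy reads a change in regional susceptibility as a change in iron deposition. An infarct, or blood products within it, inside the caudate, putamen or thalamus also changes susceptibility and is still evolving in the weeks after stroke. If those voxels stay in the regional mean, the change score mixes lesion evolution with the deposition under study.

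Three outputs are affected: the between-arm comparison, the within-group changes, and the correlations with cognitive change. The Sample size section says the substudy is mainly meant to supply effect sizes and variance components for later trials, and those are the quantities that would absorb the lesion contribution. In addition, the rationale predicts a signal on the lesion side, yet nothing in the analysis lines regions up with that side.

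**Working it through.** **1. The rules followed in order.** Enrolment at 7–30 days with any lesion site; atlas regions on both sides; mean over the whole region at both scans; unadjusted tests on the change. Mask inspection has no rule for lesioned tissue, and scan exclusion is triggered by motion. No step removes, marks or adjusts for a lesion inside a region.

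**2. Timing.** If the baseline scan falls at enrolment and the second 28 days later, the second scan is at day 7 + 28 = 35 to day 30 + 28 = 58 after onset.

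**3. How the lesion enters.** Let w be the lesioned share of a region, taken as fixed, S the susceptibility of the rest, and L that of the lesion.
- Regional mean = (1 − w)S + wL.
- Change = (1 − w)ΔS + wΔL.

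A stable lesion has ΔL = 0 and adds nothing to the change, so only its evolution matters. The correlation with cognitive change gains a term w·Cov(ΔL, Δcognition), which need not be zero if deep-grey lesions also affect cognition.

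**4. The plan's own power figures.**
- Correlation, n = 30, r = 0.50, two-sided 0.05: Φ(atanh(0.5)·√27 − 1.96) = Φ(2.854 − 1.96) = 0.81. The stated 80% reproduces.
- Between arms, 15 per arm, d = 0.8: Φ(0.8·√(15/2) − 1.96) = Φ(0.231) = 0.59; exact t, 0.56. The stated 80% does not reproduce. That is a separate matter; here 0.56 is only the reference value.

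**5. Noise between arms (illustration).** Let f be the share of participants with a lesion in a given region, and k the extra lesion-driven SD of change in units of the lesion-free SD. Both are assumptions. The SD becomes √(1 + f·k²), and d = 0.8 shrinks by that factor.

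| f | k | SD factor | effective d | power, 15 per arm |
|---|---|---|---|---|
| 0 | – | 1.00 | 0.80 | 0.56 |
| 0.1 | 1 | 1.05 | 0.76 | 0.52 |
| 0.2 | 1 | 1.10 | 0.73 | 0.49 |
| 0.2 | 2 | 1.34 | 0.60 | 0.35 |
| 0.3 | 2 | 1.48 | 0.54 | 0.30 |
| 0.3 | 3 | 1.92 | 0.42 | 0.20 |

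Dropping every participant with a lesion in the region at f = 0.2 leaves 12 per arm and power 0.47. That beats keeping them at k = 2 (0.35) but not at k = 1 (0.49).

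**6. Chance imbalance.** With independent binomial counts in 15 and 15, the probability that the arms differ by three or more lesion-bearing participants in a region is 0.12 at f = 0.1, 0.25 at f = 0.2 and 0.32 at f = 0.3.

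**7. Dilution by side (illustration).** Suppose the ipsilesional change is δ and the contralesional change is zero, the extreme case. If a share p of lesions is on the left, the left region averages pδ and the right (1 − p)δ. A left–right mean gives (δ + 0)/2 = δ/2 in everyone. At p = 1/2 all three are δ/2.

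**The case against.** **It may be settled elsewhere.** A journal article condenses, and lesion handling could sit in an imaging manual. That is possible. But the article gives the reconstruction, segmentation, extraction rule and tests in detail, and the rule it states is a mean over the region.

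**Randomisation and blinding protect the comparison.** This stands in part. A reader might infer that the arm comparison is biased. The documents do not support that: allocation is random and the image analysts are blinded, so lesion differences between arms are chance. The effect there is noise. Within-group changes and change–change correlations have no such protection.

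**Iron in affected tissue is part of the target.** This stands. A reader might infer that the regional mean measures the lesion instead of iron. That goes too far: the Discussion counts accumulation in affected as well as connected regions, and blood products contain iron. Compulsory removal of infarcted voxels could discard wanted signal, so masking belongs in a sensitivity analysis.

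**Both sides are measured anyway.** True. Naming bilateral regions does not commit the trial to averaging them, and there is no contradiction with the Discussion. What is lacking is any stated alignment to lesion side.

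**Imaging findings are already exploratory.** They are, and that limits the harm. It does not clean the variance and effect-size estimates that the substudy is meant to pass on.

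**Conclusion.** The point holds as a weakness in how the imaging endpoint is extracted and analysed. As written, lesion evolution inside a region enters the susceptibility change. It adds noise between arms and may confound the within-group changes and the correlations with cognitive change, while regions not aligned to lesion side dilute the expected ipsilateral signal.

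The size cannot be fixed from the documents, which give neither the share of participants with lesions in the regions nor any SD of change. The power range of 0.52 down to 0.20, against 0.56 without a lesion effect, rests entirely on assumed values.

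A reader might also conclude that the imaging eligibility criteria are at fault, or that excluding left-handers is wrong. The documents do not support either. The gap can be closed at extraction without restricting entry, and a wish for a homogeneous sample in analyses relating imaging to cognition is a defensible choice. The change is worth making before unblinding; it does not touch the primary clinical endpoint.

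**What to change.** Amend Neuroimaging data analysis as follows, before unblinding:

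1. The two blinded analysts who already check every segmentation also mark any infarct or haemorrhage inside each region, at baseline and week 4, on the planned T1 and gradient-echo images.
2. Analyse regions as ipsilesional and contralesional.
3. Prespecify a sensitivity analysis that repeats the between-group and correlation analyses with lesioned voxels masked out, omitting a region for a participant when most of it is lesioned. Keep the unmasked mean in the main analysis, since iron in affected tissue is part of the question.

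The cost is protocol wording and some marking work, with no added scans or visits. The sensitivity analysis will have fewer regional values, which matters at 15 per arm. Delineation would rest on T1 and gradient-echo images, the only sequences listed.

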### Sample size

This exploratory trial was primarily designed to estimate effect sizes and assess protocol feasibility. Consistent with pilot-trial recommendations for acupuncture and traditional Chinese medicine (22, 23), we set the target sample size at 30 participants per arm. Allowing for an anticipated 20% attrition, we therefore planned to enroll 36 participants in each group (total *n* = 72). For the MRI substudy, we will randomly select 15 participants per arm (*n* = 30) from the clinical cohorts, in line with Desmond and Glover’s guidance on imaging sample sizes (24). Under a two-tailed *α* = 0.05, this total sample provides approximately 80% power to detect medium-to-large correlations (r ≥ 0.50) between QSM-derived susceptibility measures and cognitive outcomes, based on Fisher’s z transformation in G*Power 3.1. Smaller associations will be interpreted with caution, and the MRI substudy is therefore primarily intended to provide preliminary estimates of effect sizes and variance components to guide the design of future, adequately powered imaging trials. With 15 participants per arm, the substudy will also have approximately 80% power to detect between-group differences in 4-week changes in regional susceptibility of approximately 0.8 standard deviations (Cohen’s d), whereas smaller treatment effects on QSM will be treated as exploratory and described descriptively.

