### Intervention and grouping

Participants will be randomly assigned to either the EA group or the sEA group. All participants will continue standard pharmacotherapy and rehabilitation during the study. Each participant will receive 20 treatment sessions (5 sessions per week for 4 weeks), each lasting 30 min.

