**Figure 2 fig2:**
[figure not shown]
Location of acupoints and non-acupoints.

After skin disinfection with 75% ethanol, sterile disposable stainless-steel filiform needles (0.25 mm × 40 mm) will be inserted. For scalp points (GV20, EX-HN1, GV24), needles will be inserted obliquely at a 15° angle to the scalp to reach the subgaleal layer, then advanced without rotation to a depth of 0.8 cun. For body points, insertion will follow standard depth and angle: PC6, LI4, ST36, and SP6 will be needled perpendicularly to a depth of 1.0 cun; GB39 perpendicularly to 0.8 cun; and LR3 obliquely to 0.8 cun. A balanced reinforcing–reducing technique will be applied to elicit the deqi sensation. EA will be delivered using the Hua Tuo SDZ-III device with four electrode pairs (GV20–GV24, left–right EX-HN1, and bilateral PC6 with auxiliary needles). Alternating sparse-dense waveforms (2 Hz/10 Hz) will be applied, with stimulation intensity set at 1–2 mA depending on patient tolerance. Identical procedures and device cues were maintained across groups to preserve blinding, while the absence of electrical output in the sEA group ensured inert stimulation.

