#### sEA group

Participants in the sEA group will receive sham acupuncture at non-acupoint, non-meridian locations situated 1–2 cun away from the true acupoints. Locations will follow the SHARE guidelines (27) and the relevant systematic review (28), with locations specified in Figure 2 and Supplementary Table S2. Needles (0.25 mm × 25 mm) will be inserted subcutaneously (scalp) or perpendicularly (body) to 0.3 cun, without manipulation or deqi. Electrodes will be placed in the same configuration as in the EA group. To maintain participant blinding, the Hua Tuo SDZ-III device will appear fully operational, with power indicators and auditory signals activated. However, the internal wiring of the electrode leads will be disconnected to ensure that no electrical current is delivered to the non-acupoints.

By using non-meridian, non-acupoint locations and superficial, non-manipulated needling, we aimed to minimize acupoint-specific effects while maintaining credibility, in line with current recommendations for sham acupuncture controls (27, 28). Nonetheless, we acknowledge that even superficial needle insertion and cutaneous stimulation may elicit non-specific sensory or segmental neuromodulatory effects, so any between-group differences are likely to represent conservative estimates of the specific effects of EA.

All treatments will be administered by physicians and therapists, who will receive protocol-specific training. Before trial initiation, they will attend a structured workshop based on a written treatment manual detailing acupoint location, needling depth and angle, manipulation, stimulation parameters, and session duration for both EA and sEA. Adherence to the protocol will be monitored via treatment logs and periodic supervision to ensure consistency across practitioners.

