### Safety evaluation

Safety monitoring will focus on adverse events (AEs) related to EA, including vasovagal reactions (dizziness, nausea, pallor, transient hypotension or syncope), intolerable needling pain, local hematoma or bruising, bleeding, infection or abscess at needle sites, needle breakage, and other post-needling reactions. All AEs will be recorded on standardized case report forms, noting the onset of time, duration, severity, relationship to the intervention, actions taken, and outcome. Serious adverse events (SAEs) will be defined according to Good Clinical Practice. Participants with repeated vasovagal episodes, severe AEs, or any SAE judged related to the intervention will discontinue study treatment and may be withdrawn if further participation is unsafe. All SAEs will be reported to the principal investigator and the institutional ethics committee within 24 h and will be managed according to the Data and Safety Monitoring procedures of West China Hospital.

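### Electronic devices are printed as an exclusion for the imaging subgroup only, so no trial-wide criterion keeps a stable carrier of an implanted device out of the arm that delivers current

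*Protocol article*

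**What the plan says.** The Exclusion criteria section of the protocol article mentions electronic devices in one place, its last item: "Imaging subgroup only: MRI contraindications (metallic implants/electronic devices) or left-handedness". The trial-wide item that comes closest to cardiac risk is "Unstable vital signs or uncontrolled severe cardiopulmonary disease". For the MRI substudy, the Sample size section states "we will randomly select 15 participants per arm", drawn from the clinical cohorts.

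On the intervention, the Intervention and grouping section says: "Each participant will receive 20 treatment sessions (5 sessions per week for 4 weeks), each lasting 30 min". In the EA group section the stimulator is used "with four electrode pairs (GV20–GV24, left–right EX-HN1, and bilateral PC6 with auxiliary needles", with an alternating 2 Hz/10 Hz waveform and "with stimulation intensity set at 1–2 mA depending on patient tolerance". In the sEA group section, "the internal wiring of the electrode leads will be disconnected to ensure that no electrical current is delivered to the non-acupoints".

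The Safety evaluation section gives the stopping rule: "Participants with repeated vasovagal episodes, severe AEs, or any SAE judged related to the intervention will discontinue study treatment". Table 1 places the eligibility screen and medical history at baseline.

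**The concern.** An implanted electronic device can matter for two separate reasons in this trial: the magnet, and the current passed through the needles. The printed criteria deal with the first and are silent on the second. Screening for implanted devices before applying electrical stimulation is a general clinical precaution. A site that followed the printed list to the letter would have no rule telling it to apply that precaution.

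What is at stake is participant safety in the EA arm. The sham leads carry no current, so the question does not arise there. The stopping rule in the Safety evaluation section acts once something has happened, whereas an entry criterion acts before exposure.

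**Working it through.** This is a reading of the criteria. The only arithmetic concerns the exposure.

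**1. Does any criterion for all participants reach a stable device carrier?**

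| Place in the protocol article | What it covers | Reaches a stable carrier? |
|---|---|---|
| Inclusion criteria: cooperation | Ability to go along with needling and testing | No |
| Inclusion criteria: stable vital signs | Current clinical state | No; a stable carrier passes |
| Exclusion criteria: "Unstable vital signs or uncontrolled severe cardiopulmonary disease" | Unstable or uncontrolled illness | No; controlled disease with a device passes |
| Exclusion criteria: organ dysfunction, systemic disease | Severe or critical illness | No |
| Exclusion criteria: last item | MRI contraindications, imaging subgroup | Names devices, but not for all participants |
| Withdrawal criteria: ineligibility found late | Patients who should not have been enrolled | No; under the printed list the carrier is eligible |
| Safety evaluation: named adverse events | Needling reactions | Device interference is not named |

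**2. What does the imaging item do for a carrier?** Substudy members are drawn from the clinical cohorts and the item is confined to the imaging subgroup. A carrier who is drawn is therefore not scanned. Nothing printed then removes that person from EA. So the item screens nobody for electrical stimulation, whether or not they are drawn for MRI.

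**3. What is the exposure in the EA arm?** Inputs are from Intervention and grouping and from EA group.
- Sessions: 5 per week × 4 weeks = 20, which matches the stated 20.
- Needling session time: 20 × 30 min = 600 min, or 10 hours per participant over the course.
- Intensity: 1–2 mA, limited by tolerance.
- Electrode pairs: GV20–GV24 (1) + left–right EX-HN1 (1) + one at each PC6 with its auxiliary needle (2) = 4, which matches the stated four. On this count no pair runs from one forearm to the other. The sentence does not spell this out, so it is a reading and not a stated fact.

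**4. Can the number of carriers or the risk be computed?** No. The documents give neither a device prevalence in this population nor an interference risk at these settings. The number of carriers who would be enrolled could be zero.

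**5. Effect on the statistics.** None. The 36 per arm, the significance level and the planned analyses stay as they are.

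**The case against.** The best counter-argument is that this is something left unprinted and not something stated wrongly. The item is correct for MRI, the section introduces its list in words that need not mean it is complete, and neither the full protocol nor the treatment manual is shown. That carries some weight, and it is why the point is confined to the criteria as printed. It does not dispose of the point. The authors did consider electronic devices, wrote a criterion for them and limited it with the word *only*. A trial-wide device exclusion in an unseen document would conflict with that limit, or at least make the device part of the item redundant. The treatment manual is described as covering needling and stimulation technique, not eligibility.

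A second objection is that practical safeguards exist. Participants are inpatients of one department, medical history is taken, Table 1 marks MRI at baseline in a column headed with all 72 participants, and trained physicians and therapists give the treatment. Current is low and the pairs appear local. All of this stands and lowers the concern. It makes it likely that a device would be noticed, but no printed rule says what to do then.

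A third objection is that the hazard is not in the documents. This too stands as far as size is concerned: the point can be made only as a precaution.

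A reader might also infer a headline count: 72 / 2 = 36 in the EA arm, less 15 in the substudy, leaves 21 (58%) without device protection. The documents do not support that split. The 15 are not protected from stimulation by the item; they are merely free of devices because they were scanned. Nor would 21 be a count of people who have a device.

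**Conclusion.** The point holds as a gap in the scope of a printed eligibility rule. As written, electronic devices bar a patient from imaging and not from EA, and no other criterion bars a stable carrier from being randomised to an arm with up to 10 hours of sessions at 1–2 mA.

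Its size is not quantified and should not be presented as if it were. A reader might go further and infer that participants are being put at known risk. The documents do not support that: they give no interference risk, and the electrode layout appears to keep current local to the scalp and each forearm. The conclusion rests on two assumptions: that the printed criteria are the ones applied at screening, and that checking for implanted devices before electrical stimulation is sensible practice. It has no bearing on the estimate, the power or the analysis.

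**What to change.** Split the last exclusion item in two:

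- *All participants:* active implanted electronic device (for example pacemaker, implantable defibrillator or neurostimulator), checked at the baseline medical history and before randomisation.
- *Imaging subgroup only:* other MRI contraindications, including metallic implants, and left-handedness.

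The exclusion should apply to both arms, even though only EA delivers current, because eligibility has to be settled before allocation is known.

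The cost is one line of wording and one question at a visit that already takes a medical history. The downside is that any otherwise eligible carriers are not enrolled and the results would not extend to them. The documents do not allow their number to be estimated. If the full protocol already screens for devices, the article's criteria need only be brought into line with it.
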